### Primary health outcome

The primary outcome of the study is reduction in diarrheal incidence (cases per 1000 child-week), prevalence and average duration (days per episode) in children under four. To measure progress, the mother or caregiver of each household will record the diarrheal episodes of the youngest child under four on a daily basis using the ‘Sanitation Calendar’ (Fig. 4). The Sanitation Calendar will enable us to look into the intervention’s effects on incidence density as well as the duration of diarrhea in children under four. A 7-day recall period will be used to measure diarrheal prevalence.

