### Sample size calculation

Based on the findings of the preliminary survey, we estimated diarrhea prevalence in Idiofa Territory to be 10%. We also made an assumption that the intervention would reduce the prevalence by 2.5% (25% relative reduction) on the basis of systematic reviews. Unlike the previous studies, we calculated sample size on the basis of *Incidence density of diarrhea by ‘child-weeks’* using formula [28] as follows:

The expected value of s^2^ is given by:

E(s^2^) = *λ* Av(1/y_j_) + *σ*
^2^
_c_ = *λ*Av(1/y_j_) + k^2^
*λ*
^2^,where λ is the true mean rate, y_j_ is the child-weeks of follow up in the j^th^ cluster, Av(1/y_j_) indicates the mean over all m clusters, σ^2^
_c_ is the between-cluster variance of true rates, and k is the coefficient of variation of those rates (22). Using the preliminary survey, we were able to determine that the overall diarrheal rate for the 20 *quartiers* was 0.1 (or 10 per 100 child-weeks). The empirical standard deviation of the observed diarrhea rates was s = 0.051216, and the average of the reciprocal child-weeks per *quartier* was Av(1/y_j_) =0.022222, so that k was estimated as follows:$$ {\widehat{\sigma}}^2=0.0{51216}^2\hbox{--} \mathrm{0.10.022222}=0.000401,\mathrm{therefore},\mathrm{k}=\surd \left(0.000401/0.1\right)=0.063 $$

With an assumption that the diarrhea rate in control *quartiers* remains constant at λ_0_ = 0.1, we required 80% power (z_β_ = 1.96) if the intervention is to reduce the diarrhea rate by 25% to λ_1_ = 0.10×0.75=.075. Assuming y = 540 child-weeks of observation in each *quartier*, the number of *quartiers* required in each treatment group is given by:$$ \mathrm{c}=1+{\left(1.96+0.84\right)}^2\left[\left(0.1+0.075\right)/540+{0.063313}^2\left({0.1}^2+{0.075}^2\right)\right]/{\left(0.1-0.075\right)}^2=6.14 $$

Ignoring clustering, y = (1.96 + 0.84)^2^(0.1 + 0.075)/(0.1–0.075)^2^ = 2195.2 child-weeks per group, corresponding to 2195.2/540 = 4.07 *quartiers*. Thus, the expected design effect for this trial would be 6.14/4.07 = 1.51.

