### Data analysis

Intention-to-treat analysis will be conducted to explore how well-equipped latrines reduce diarrhea incidence. To this end, the incidence density of diarrhea in children under four (diarrheal incidence per child-week, per child-month) and the reported diarrheal prevalence of the 7-day period will be calculated. Also, for other age groups (6–19, 20–39, 40 years and above), the reported diarrheal prevalence of the 7-day period will also be calculated. Generalized estimating equations will be used for the investigation at the cluster level. A log-binomial model will be used for calculating the incidence rate of diarrhea. The Random Effects model will be used, taking account of between-cluster variation based upon the assumption that there are cluster-level effects. Per-protocol analysis also will be conducted only as a contingency measure in cases where the coverage of latrines remains at an unexpectedly low level by the time when the intervention is completed. However, if we employ a per-protocol analysis, we cannot quantify the effects of well-equipped latrines, as this would break the comparability between the control and intervention groups obtained from randomization. Instead, we would note that per-protocol analysis is only an auxiliary analysis method to give additional background information. In addition, multi-level analysis will be conducted to investigate whether children living in the households without latrines could benefit from herd protection when a *quartier* reaches a certain level of latrine coverage (for instance, 70%).

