In addition, the Sanitation Calendar is to be used as an effective method of tracking diarrhea for a registered child. With the Sanitation Calendar, the incidence density of diarrhea can be calculated by dividing diarrhea cases by observed child numbers multiplied by the specific duration observed (e.g. week, month, etc.). This would be a more effective tool since it would cause less fatigue among the respondents, who would otherwise be asked to provide information about their children’s diarrheal episodes on a daily basis by interviewers. Assuming that the incidence of diarrhea among children is three times a year on average [32], the number of days marked ‘O’ in mothers’ diaries will not be very high. As for the duration of diarrhea, it was estimated at 10–20 days on average. Except for the days marked with ‘O,’ all the other days will be considered ‘X’. The Sanitation Calendar allows the day-to-day observation of diarrhea and resolves the limitations associated with the small number of clusters in the trial. Previous studies were unable to identify the effect of improved sanitation on diarrheal duration because they relied on the period prevalence of reported diarrhea. The utilization of the Calendar will enable us to explore a relationship between sanitation improvements and diarrhea and investigate the extent to which well-equipped and appropriately managed latrines affect disease duration. The measurement relying on caregivers’ reports, which are subjective in nature, is one of the limitations of this study. As we will not be able to conduct laboratory tests to assess children’s diarrhea incidence, there may be under-reporting or over-reporting of diarrhea. Despite this risk, we do not expect any significant difference of reporting patterns between the people of the intervention and control *quartiers*.

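### A log-binomial model with no stated yes/no unit is assigned to the incidence rate, although that outcome is episodes per child-week

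*Protocol article*

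**What the plan says.** Under Data analysis, the article plans to calculate "the incidence density of diarrhea in children under four (diarrheal incidence per child-week, per child-month") together with a 7-day reported prevalence. It then states: "A log-binomial model will be used for calculating the incidence rate of diarrhea". No yes/no unit, offset or person-time term is given. The same paragraph names generalized estimating equations for the cluster-level investigation and adds "The Random Effects model will be used, taking account of between-cluster variation".

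Other sections define incidence as a rate:

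- Primary health outcome lists "reduction in diarrheal incidence (cases per 1000 child-week), prevalence and average duration (days per episode) in children under four", so incidence, prevalence and duration are separate components.
- The Discussion says that "the incidence density of diarrhea can be calculated by dividing diarrhea cases by observed child numbers multiplied by the specific duration observed". It also expects about three episodes per child per year, each lasting 10 to 20 days on average.
- Sample size calculation uses a formula for rates. The overall rate in the preliminary survey "was 0.1 (or 10 per 100 child-weeks"), and the target is a 25% reduction to 0.075.

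Follow-up will be unequal. Newborns join an open cohort (Eligibility criteria and enrollment), and 12.5% loss is allowed for (Sample size calculation). The diary marks each day with or without diarrhea for 12 months (Health outcomes assessment, sanitation calendar).

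**The concern.** A log-binomial model describes the probability that a yes/no unit is positive. The incidence outcome is a count of recurrent events over child-time. The two meet only after the data have been cut into binary units, and the article does not say how. Candidate units are the child-week, the child-month (both named in the same paragraph) and the child. Within a week, positive could mean that an episode began or that any day was marked with diarrhea.

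These choices give different effect measures from the same diaries. If the unit is left open, it can be chosen after the data are seen, and the reported effect may not be the rate ratio for which the trial was sized. If weeks are coded by any diarrhea day, the incidence result also absorbs duration, although separating the two is a stated reason for the diary. The model would fit the 7-day prevalence, but the sentence attaches it to the incidence rate.

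**Working it through.** **Inputs.** From Sample size calculation: control rate 0.1 and intervention rate 0.075 per child-week, 540 child-weeks per quartier, k = 0.063313, and at least 12 weeks of follow-up. From the Discussion: three episodes a year, 10 to 20 days each. Assumption: onsets follow a Poisson process with constant rates.

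**Step 1: the plan's own figures.** Ignoring clustering, (1.96 + 0.84)² × (0.1 + 0.075) / 0.025² = 7.84 × 0.175 / 0.000625 = 2195.2 child-weeks per group, as printed. With clustering, the printed inputs give 1 + 7.84 × (0.175/540 + 0.063313² × 0.015625) / 0.000625 = 5.85, not the printed 6.14. That gap is a separate matter. What counts here is that both formulas use rates and child-weeks, so the design effect measure is 0.075/0.1 = 0.75.

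**Step 2: what a log-binomial model would estimate.** For a unit of t weeks, positive if at least one onset occurs, p = 1 − exp(−rate × t), and the ratio is p(intervention)/p(control).

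| Yes/no unit | t (weeks) | Control | Intervention | Ratio | Reduction |
|---|---|---|---|---|---|
| Child-week with an onset | 1 | 0.0952 | 0.0723 | 0.759 | 24.1% |
| Child-month with an onset | 4.35 | 0.3526 | 0.2783 | 0.789 | 21.1% |
| Ever/never per child, 12 weeks | 12 | 0.6988 | 0.5934 | 0.849 | 15.1% |

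At three episodes a year (3/52.18 = 0.0575 per child-week), the same ratios are 0.755, 0.773 and 0.811.

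**Step 3: does the child-week lose repeat episodes?** A day-by-day simulation used 100,000 children per arm over 12 weeks. With episodes of 10, 15 or 20 days, no child-week held two onsets. The proportion of weeks with an onset therefore equalled episodes per child-week, and the two ratios were identical (0.771, 0.782 and 0.790). They differ from 0.75 because 0.1 and 0.075 were set per diarrhea-free week while the denominator was all child-weeks. That is a denominator effect and is the same for either model. With 3-day episodes the ratios were 0.752 (rate) and 0.756 (onset weeks).

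**Step 4: weeks coded by any diarrhea day.** An episode of d days starting on a random weekday touches on average 1 + (d − 1)/7 = (d + 6)/7 calendar weeks. This is 16/7 = 2.3 for 10 days and 26/7 = 3.7 for 20 days.

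To see the mixing, assume an equal onset rate of 0.1 per week at risk in both arms, but durations of 15 days (control) and 10 days (intervention). The probability of a diarrhea-free week is exp(−0.1) / (1 + 0.1 × d/7):

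- 15 days: 0.9048/1.2143 = 0.745, so the risk of a positive week is 0.255.
- 10 days: 0.9048/1.1429 = 0.792, so the risk is 0.208.

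The ratio is 0.208/0.255 = 0.82, an apparent 18% reduction in incidence with no change in the onset rate. The two durations are an illustration and do not come from the article.

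**The case against.** The best defence is that the article does point to a unit. It expresses incidence per child-week more than once and calls child-weeks the unit of the denominator. With one record per observed child-week, repeat episodes in different weeks are each counted, unequal follow-up enters through the number of records, and the ratio is 0.759 against 0.75. The daily diary identifies onset days, so new-onset weeks can be coded and duration measured separately. All of this stands, and under that coding the model does little harm. But the article does not say that this is the coding, and it also names the child-month.

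A reader might go further and infer that the log-binomial model would necessarily give an attenuated effect, nearly vanishing over a year: ever/never over 12 months gives 0.985 at 0.1 per week and about 0.94 at three episodes a year. The documents do not support that. No section proposes collapsing each child to ever/never. A constant ratio over 12 months also sits badly with the phase-in described under Study design, where the control arm receives the intervention after the 8-month first phase. Likewise, coding by any diarrhea day is possible but not stated, and if durations are equal in the two arms the multiple counting largely cancels from the ratio.

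Naming both generalized estimating equations and a random-effects model is a minor matter. The text does not say that they serve the same comparison, and with a log link and a random intercept independent of arm the marginal and conditional ratios coincide. Which one is primary can be left to an analysis plan.

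**Conclusion.** The mismatch is real: a probability model without a stated yes/no unit is assigned to an outcome that is defined and sized as a rate with recurrent events. The effect on the result is conditional. Against a design rate ratio of 0.75 it runs from negligible (0.759, new-onset child-weeks) through modest (0.789, child-months) to material (0.849, ever/never over 12 weeks, and closer to 1 with longer follow-up). Coding by any diarrhea day would blur incidence with duration. These figures rest on Poisson onsets at constant rates. Attenuation is a possibility that the wording leaves open and is not an established consequence. The sentence concerns a primary outcome component and should be corrected, but it does not invalidate the trial.

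**What to change.** Replace the sentence so that new episodes are analysed with a Poisson or negative binomial model, with log(observed child-time at risk) as offset. This gives an incidence rate ratio and should account for clustering and the randomization strata. Say whether days with diarrhea are removed from the time at risk, since step 3 shows that this moves the ratio. Keep the log-binomial model for the 7-day prevalence. If the log-binomial model is retained for incidence, the minimum is to state that it is fitted to child-weeks with a new onset.

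The model change costs a sentence or two and uses diary data already planned. Accounting for clustering is not free. Under Study design, allocation was by three strata of two groups, so there are six allocated groups. Clustering at that level leaves about 6 − 3 (strata) − 1 (arm) = 2 degrees of freedom, and the level chosen should be stated with that consequence in view.

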## Discussion

This trial aims to investigate the effects of well-equipped latrines when reaching up to a universal or sufficient level, rather than exploring the behavioral factors for latrine improvement. Recent studies [14, 15] with the same purpose failed to reach a universal or sufficiently high coverage level despite employing rigorous methodology; therefore the results can hardly indicate the true effects of high latrine coverage. For this reason, to come up with a solution to achieve the sufficiently high level of coverage, we paid close attention to the lessons learned from a study conducted in Bangladesh [31], whose results suggested that subsidies could increase latrine ownership both in subsidized and unsubsidized households. In the trial, material subsidies will be provided to all households in the intervention arm who complete the latrine improvement activities (e.g. digging a 1.5 m-deep pit, installing a superstructure and roof) in contrast to the selective subsidy provision in previous studies [14, 15]. It is critically important to mobilize community members to reach sufficient sanitation coverage. SNHR officials take on the responsibility to educate community members on the importance of improved latrines and encourage them to participate in the collective efforts to increase latrine coverage at the *quartier* level, and mobilize locally available materials and unskilled labor voluntarily to construct their household latrine.

The project will be effectively monitored through the ‘Sanitation Map’. The WASH committee will visit each household to monitor the latrine uptake progress and to draw the Sanitation Map for each *quartier* on a monthly basis (Fig. 6). The WASH committee drew a draft version of a Sanitation Map on a pilot basis in the run-up to the intervention (June 2015), and it was found that the WASH committee understood the objectives of sanitation mapping well enough for the project implementer to monitor progress. The Sanitation Map will be continuously updated through the early, middle and final stage of project implementation, both in the intervention and control arms.

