**Discussion:**

Material subsidies will be provided only to the households who complete pit digging plus superstructure and roof construction, regardless of their income level. This study employs a Sanitation Calendar so that the mother of each household can record the diarrheal episodes of her under-four child on a daily basis. The diary enables examination of the effect of the sanitation intervention on diarrhea duration and also resolves the limitation of the small number of clusters in the trial.

In addition, the project will be monitored through the ‘Sanitation Map’, on which all households in the study area, including both the control and intervention arms, are registered. To avoid information bias or courtesy bias, photos will be taken of the latrine during the household visit, and a supervisor will determine well-equipped latrine uptake based on the photos. This reduces the possibility of recall bias and under- or over-estimation of diarrhea, which was the main limitation of previous studies.

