### Project implementation

KECO will be responsible for supervision and management of the project implementation. Two sanitation experts have been deployed to this project team from the WSA to provide technical advice and three sanitation officials from SNHR have been seconded to facilitate community mobilization and provide information about the local culture, such as social norms and, if any, taboos during the project period.

Before the intervention, WASH committees were established right after 18 *quartiers* had been selected for the target area of the water supply program in February 2015; therefore, the committees were present in both the intervention and control arms. Nine WASH committee members were elected by the people living in each *quartier*. It was recommended that they elect at least three female members, but several *quartiers* could not recruit at least three female members to form their committee. The main roles and responsibilities of the WASH committee with regard to the water supply program are to maintain water facilities and collect water fees from the *quartier* residents. Later on, after 9 *quartiers* were selected for this sanitation intervention, we added new roles and responsibilities of the committee for latrine improvement for the intervention group and trained the committee members to perform those tasks. The new roles and responsibilities of the WASH committee are defined as (1) community mobilization on latrine improvement; (2) educating community people for healthier hygienic practices; (3) drawing and regularly updating the Sanitation Map; (4) monitoring the progress, especially on the ‘recording status of the Sanitation Calendar’ and ‘latrine improvement situation’ at the household-level in each *quartier*.

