**Fig. 6 Fig6:**
[figure not shown]
Sanitation map of Ingundu quartier (Draft version, June 2015), Sanitation map of ImpiniNsi quartier (Draft version, June 2015) - are correctly shown

All the 7286 households on the Sanitation Map will be assigned an identity number and marked with a color. They will be marked red when the household latrine does not improve, green when the latrine improves, and yellow when the latrine is under construction. The Sanitation Map can help the WASH committee as well as community members check the progress not only of the *quartier* they belong to, but also of the other groups. Community members will be educated on the herd protection effects of well-equipped latrines and also the importance of the 80% target for latrine coverage. If a *quartier* reaches 80% well-equipped latrine coverage, it will be certified as a ‘Healthy *quartier*’ and rewarded by the project implementer. The sanitation mapping is expected to create peer pressure within and among the *quartiers,* sparking ‘healthy’ competition that will expand the rate of coverage.

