The degree of latrine improvement will be scored according to the well-equipped latrine criteria. This will allow us to assess whether and how the diminishing effect of well-equipped latrines on diarrhea incidence among children under four differs depending on the degree of latrine improvement. Previous studies [14, 15] exploring the health benefits of sanitation have not paid attention to the possibility that the effect of latrines might vary depending on the degree of their improvement. Although a recent trial [21] reported an increase in access to one’s own latrine from 33 to 64.8% in rural Mali, they found no effect of a community-led sanitation improvement on the children’s diarrhea. Based on the 5-f theory, the Joint Monitoring Programme defines an “improved sanitation facility as one that hygienically separates human waste from human contact,” highlighting the importance of accounting for improvement status of latrines. In the case of pit latrines, the existence of a slab and hand-washing facilities, pit-hole depth and number of flies could be considered criteria for identifying the improved status of latrines. Applying these criteria, the proportion of improved latrines in Pickering et al. (i.e., latrines with concrete slabs) would be reduced to less than 30%. Focusing solely on the presence or access to any latrine type may mask the genuine health benefits of improved latrines.

The study hypothesis was not disclosed to people subject to the trial, though the general objectives were explained to them when obtaining informed consent. Thus, people are highly unlikely to be aware of the arm to which they belong because the sanitation intervention will continue to be executed in the control arm during the second phase. We thus surmise that the underreporting of diarrheal prevalence among the caregivers with a household latrine will not be a serious problem in this study. However, the limitation of not blinding still remains in this study since having a latrine is explicit in itself and many of the WASH committee members in the control arms were aware of the intervention even from the beginning due to their participation in the community lottery activity for random allocation.

Since the trial’s randomization process yielded remarkably balanced results between the two arms, and since no other intervention is expected to roll out until February 2017, any differences observed in diarrheal incidence can be attributable to latrine improvement.

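### The Sanitation Map, which the plan expects to raise latrine uptake, runs in both arms with no stated limit on its promotional functions in control quartiers before their phase

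*Protocol article*

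**What the plan says.** **Who runs the Map, and when.**
- Study design confines the well-equipped latrine project to the intervention arm for a first phase of 8 months. Controls follow after the second survey (January 2016).
- Project implementation says that new latrine-improvement roles were added to the committees of the intervention group. The list includes "3) drawing and regularly updating the Sanitation Map".
- The Abstract describes the Map as one "on which all households in the study area, including both the control and intervention arms, are registered".
- The Discussion has committees visit households and draw the Map monthly for each quartier, and adds: "The Sanitation Map will be continuously updated through the early, middle and final stage of project implementation, both in the intervention and control arms". The Discussion later dates the early stage of the intervention to July and August 2015, which is inside the first phase.

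**What the Map is for.** The Discussion text after Fig. 6 gives it a purpose beyond measurement:
- "All the 7286 households on the Sanitation Map will be assigned an identity number and marked with a color": red for not improved, yellow for under construction, green for improved.
- "The Sanitation Map can help the WASH committee as well as community members check the progress" of their own quartier, "but also of the other groups".
- "The sanitation mapping is expected to create peer pressure within and among the" quartiers, with competition that is meant to widen coverage.
- A quartier that reaches 80% well-equipped coverage is certified and rewarded.

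None of these four functions is limited to an arm or a phase.

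**Awareness of allocation.** The Discussion states that "people are highly unlikely to be aware of the arm to which they belong".

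**The concern.** The trial's question depends on a large difference in latrine coverage between arms while controls are still untreated. By the plan's own reasoning, mapping raises uptake. If its promotional functions operate in control quartiers during the first phase, controls receive part of the intervention early, their latrines may improve early, and the estimated effect moves towards no difference. The sample size calculation makes no allowance for this, since it holds the control rate constant at 0.1 per child-week.

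The second issue is awareness. The primary outcome is recorded by the mother or caregiver. Residents who can compare their quartier's colours with those of other groups have a means of working out their arm. That weakens the statement that they are unlikely to know it, and the related expectation that reporting will not differ between arms.

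**Working it through.** **1. The sections side by side.**

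| Question | Study design / Project implementation | Abstract / Discussion |
|---|---|---|
| Who draws the Map? | Listed as a role added for intervention-group committees | Drawn for each quartier, updated in both arms |
| When? | Latrine project in the intervention arm only during phase 1 | Early, middle and final stages; early stage is July–August 2015 |
| Monitoring or promotion? | Listed beside mobilisation, education and progress monitoring | Introduced as monitoring, then expected to produce peer pressure and competition |
| Are colours, comparison, 80% target and reward limited by arm? | Not stated | Not stated |

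A control-arm committee could not tell from this whether to draw the Map before phase 2 or, if it does, whether to show it to residents.

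**2. Illustration of dilution.** The document gives no control uptake for phase 1, so the figures in this step are assumptions.

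Inputs from the document: control rate 0.1 and intervention rate 0.075 per child-week (25% reduction; Sample size calculation); improved-latrine coverage 0% in both arms at baseline (Table 1); 80% coverage target (Discussion). Assumptions: the intervention arm reaches 80%, controls reach 10–20%, and the effect is proportional to coverage.

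Fraction of the effect obtained by controls: f = control coverage / 80.
Control rate: λ0 = 0.1 × (1 − 0.25 f).

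- 10% coverage: f = 0.125; λ0 = 0.096875; rate ratio 0.075/0.096875 = 0.774; reduction 22.6%.
- 20% coverage: f = 0.25; λ0 = 0.09375; rate ratio 0.075/0.09375 = 0.800; reduction 20.0%.

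Scaling the 25% directly by the coverage difference (25% × 70/80 = 21.9%; 25% × 60/80 = 18.8%) overstates the loss, because it leaves out the fall in the control rate, which is the denominator.

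**3. What this would do to power.** The plan's formula is c = 1 + (1.96 + 0.84)² [(λ0 + λ1)/y + k²(λ0² + λ1²)] / (λ0 − λ1)². With its printed inputs (0.1, 0.075, y = 540, k = 0.063313) it gives 1 + 7.84 × (0.00032407 + 0.00006263)/0.000625 = 5.85, not the printed 6.14. That discrepancy is a separate matter.

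Inverted for 9 quartiers per arm:
power = Φ{ √[8(λ0 − λ1)² / ((λ0 + λ1)/y + k²(λ0² + λ1²))] − 1.96 }.

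| Control coverage | Reduction | Power, k = 0.063313 (as printed) | Power, k = 0.20 |
|---|---|---|---|
| 0% | 25.0% | 94.9% | 63% |
| 10% | 22.6% | 88.9% | 53% |
| 20% | 20.0% | 78.7% | 43% |

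The last column uses k = √0.000401/0.1 = 0.20, which follows from the plan's own definition of k as the coefficient of variation. The absolute level of power depends heavily on k, so only the direction and rough size of the drop should be read from this table.

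**The case against.** **Mapping both arms is not in itself a flaw.** Coverage in control quartiers is needed to document the contrast, and the planned herd-protection analysis needs coverage by quartier. This stands, and the fix keeps that data collection.

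**The role list may simply be loosely worded.** It also contains monitoring of the Sanitation Calendar, although the Calendar goes to every registered household. This is plausible. It softens the contradiction over who draws the Map, but does not settle which functions operate in controls.

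**A reader might infer that the competition, the 80% target and the reward are delivered to controls in phase 1, or that control households are marked in public.** The document does not say so. It is silent on arm and phase, it does not describe a public display, and it does not define the other groups as the other arm. Subsidies are tied to the intervention arm, and mobilisation and education are among the roles added for the intervention group.

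**A reader might also infer that the contrast does shrink.** That is not established. A well-equipped latrine needs all six elements, and the cement slab, pit-hole cover and hand-washing facility are the subsidised items. The 68.0% of control households with an unimproved latrine would therefore not readily qualify. The trial also presumes that sufficient coverage is needed for protection; on that premise, 10–20% coverage in controls might change their diarrhoea very little. Against this, the plan cites evidence of gains in unsubsidised households and expects a social multiplier, and it will examine effects by degree of improvement, so partial upgrades could matter.

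**Lack of blinding is already conceded.** The Discussion accepts that latrines are visible and that many control-arm committee members knew of the intervention from the allocation lottery. Closing the Map would cure neither. What remains is that the Map could carry this knowledge to caregivers. Any resulting difference in reporting could also bias away from the null, against the direction of contamination.

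**Conclusion.** The point holds as an unresolved inconsistency with a plausible consequence. The document places the Map in both arms during the phase reserved for the intervention arm, describes it as a means of raising coverage, and does not say which of its functions are withheld from controls. Dilution towards no difference is therefore possible, and residents may be better able to infer their arm than the plan states.

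It is not shown that controls are offered the reward or competition in phase 1, that contamination will occur, or how large it would be. The 20–23% figure rests on an assumed control coverage of 10–20%, an assumed 80% in the intervention arm, and proportionality between coverage and effect; the document supports neither the first assumption nor the third. The change is still worth making, because it protects the contrast on which the trial rests at very little cost.

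**What to change.** Reconcile Project implementation with the two Discussion paragraphs on the Map, and state that:

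- until the control phase starts, the control-arm Map is a closed data-collection record, holding latrine photos and status for committees and supervisors only;
- during that time control quartiers have no community display or colour feedback, no comparison with other quartiers, no 80% target and no certification or reward;
- display, comparison, competition and certification are intervention components, run only in the arm currently receiving the intervention.

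The cost is protocol wording and an instruction to committees. The same coverage data are collected in both arms. The one small downside is that control residents have no map feedback until their own phase. The Discussion's statement on awareness of allocation should also be qualified to acknowledge the Map as a possible route to that knowledge.
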